Intracardiac echocardiography (ICE) is routinely used during AF ablation procedures for transseptal puncture guidance and complication monitoring. Emerging evidence suggests that ICE, when performed from appropriate positions such as the pulmonary artery or right ventricular outflow tract, may allow for reliable detection of LAA thrombi. Studies by Di Biase et al., involving over 7,000 patients undergoing uninterrupted anticoagulation and AF ablation, demonstrated the safety and feasibility of using ICE as an alternative to TEE for preprocedural thrombus screening. A recent retrospective study also showed that ICE provides comparable thrombus detection and complication rates, with added advantages such as lower post-procedural fever and improved hospital efficiency. However, these findings are derived from retrospective or non-randomized studies, limiting the strength of the evidence.

In the ICE-CHIP trial, ICE showed lower sensitivity for LAA thrombus detection compared to TEE, likely due to the limited imaging range as the catheter remained in the right atrium. With advancements in imaging technology and catheter positioning, ICE can now offer high-resolution visualization of the entire LAA, enabling its use as a potential replacement for TEE. While recent consensus documents from EHRA/HRS and China acknowledge the potential of ICE to replace TEE in LAA thrombus assessment, the recommendation remains weak due to the lack of randomized controlled evidence.

Therefore, we designed this prospective, multicenter, randomized controlled trial to systematically evaluate the diagnostic performance, safety, and clinical utility of ICE versus TEE in LAA thrombus screening before AF ablation. This study aims to fill the current evidence gap and provide high-level clinical data to support guideline recommendations and optimize procedural workflows.

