### 2. Minimized Fluoroscopy Strategy:

- During procedures utilizing the ICE catheter, a strategy of minimized fluoroscopy was employed, although achieving zero radiation exposure was not mandatory.
- Specifically, ICE catheter and CARTSOUND™ integrated real-time ICE imaging were utilized for:
  - Geometry construction
  - Transseptal puncture
  - Effusion monitoring

319                   ○ Minimal fluoroscopy was utilized at each step as determined feasible  
320                   by the individual operator.

321 This approach ensures comprehensive imaging while minimizing patient exposure to  
322 radiation. The use of real-time ICE imaging facilitates precise procedural guidance  
323 and enhances safety during complex cardiac interventions.

324

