### 325 **TEE Group (Control Arm)**

- 326           • Thrombus screening performed within 24 hours pre-procedure using standard  
327           TEE (GE Vivid E9 or Philips iE33).
- 328           • Multiplanar views including mid-esophageal four-chamber view, mid-  
329           esophageal two-chamber view, mid-esophageal long-axis view, transgastric  
330           short-axis view, deep transgastric long-axis view and upper esophageal aortic  
331           arch view.
- 332           • Transseptal puncture guided by fluoroscopy.

333

334 TEE images were first evaluated by an experienced echocardiographer and  
335 subsequently reviewed by at least two other experienced echocardiographers who  
336 were blinded to the results of the initial TEE. This meticulous procedure ensures  
337 comprehensive cardiac assessment and quality control through multiple expert  
338 reviews.

339

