## Secondary Endpoints

The prespecified secondary endpoints include:

- The detection rate of thrombus.
- Death related to the radiofrequency ablation procedure.
- Major bleeding complications: pericardial effusions and cardiac tamponade.
- Minor bleeding complications: vascular complications such as pseudoaneurysms, arterio-venous fistulas, and hematomas.
- Procedural characteristics: total procedure time, fluoroscopy time, and radiofrequency delivery time.
- Pre-procedural psychological state: Assessed using the Hospital Anxiety and Depression Scale (HADS), 14a self-assessment questionnaire measuring anxiety and depression levels in patients receiving medical care. Higher scores indicate more severe symptoms.
- Procedural pain degree: Measured using the Numeric Rating Scale (NRS), where patients rate their pain on a scale from 0 (no pain) to 10 (worst possible pain).
- Hospitalization cost: Expenses incurred during a patient's hospital stay, including charges for medical services, procedures, medications, accommodations, and other related expenses.
- Preprocedural waiting time: The period of time a patient waits before undergoing ablation.

These well-defined endpoints will help the researchers assess the effectiveness, safety, and patient experience of using ICE compared to TEE in patients undergoing AF ablation.

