#### 440 **Outcome and Follow-Up Data**

- 441       • Thromboembolic events (stroke, TIA, systemic embolism)
- 442       • Complications: bleeding, tamponade, vascular injury
- 443       • Pain and anxiety scores (NRS and HADS)
- 444       • Hospitalization cost and duration
- 445       • Follow-up visits at 1 week, 2 weeks, and 1 month post-procedure

- Adverse events and serious adverse events (SAEs)

All collected data are entered in real time or within 14 days of each study visit, and validated by the site principal investigator.

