#### **Secondary Endpoint Analysis**

- 508 • Continuous variables (e.g., procedure time, pain scores): Presented as mean  $\pm$   
509 SD or median (IQR); Compared using t-test or Wilcoxon rank-sum test  
510 (based on normality).
- 511 • Categorical variables (e.g., thrombus detection, bleeding): Expressed as counts  
512 and percentages and compared using chi-square or Fisher's exact test.
- 513 • Binary secondary endpoints were reported as relative risk (RR) with 95% CIs;  
514 continuous endpoints were expressed as mean difference (MD) with 95% CIs.
- 515 •

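### Major bleeding counts pericardial effusions with no severity threshold, and the protocol specifies effusion monitoring only in the ICE arm, so the relative risk may be tilted against ICE

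*Protocol*

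**What the plan says.** Protocol section 3.5 (Secondary Endpoints) lists "Major bleeding complications: pericardial effusions and cardiac tamponade". It gives no size, symptom, drainage or haemodynamic threshold.

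Section 3.4 treats the arms differently during the procedure. In the ICE arm (Minimized Fluoroscopy Strategy), the "integrated real-time ICE imaging were utilized for" three purposes, one of which is "Effusion monitoring". The TEE arm has "Thrombus screening performed within 24 hours pre-procedure using standard" equipment, and then "Transseptal puncture guided by fluoroscopy". The ablation procedure common to both groups names no effusion check.

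Section 5.1 collects "Complications: bleeding, tamponade, vascular injury" and schedules visits at 1 week, 2 weeks and 1 month. It names no echocardiogram at any of them.

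Section 5.4 (Secondary Endpoint Analysis) states that "Binary secondary endpoints were reported as relative risk (RR) with 95% CIs", with a chi-square or Fisher's exact test.

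Sections 4.2 and 6.1 provide a blinded Clinical Endpoint Committee, which adjudicates suspected thromboembolic events and major complications under its own charter. Care providers are not blinded.

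**The concern.** An effusion that causes no symptoms enters the data only if someone images the pericardium. As worded, the endpoint admits such effusions, and the protocol provides the imaging in one arm only. The protocol itself regards ICE as a detector: section 2.1 describes it as "routinely used during AF ablation procedures for transseptal puncture guidance and complication monitoring".

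If detection differs between arms, the relative risk mixes two things: how often effusions occur and how often they are found. With equal true rates it would show an apparent excess under ICE. With a truly lower rate under ICE, it could hide the benefit. This is the protocol's only major-bleeding endpoint, in a trial whose title announces a comparison of periprocedural complications.

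**Working it through.** **Step 1: the text, arm by arm.**

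| Opportunity to find an effusion | ICE arm | TEE arm |
|---|---|---|
| Before ablation | ICE thrombus screening | TEE within 24 hours before; cannot show an effusion caused by ablation |
| During ablation | Real-time ICE, effusion monitoring a listed use | None named |
| After ablation and at follow-up | None named | None named |

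The arms differ in the second row. The protocol does not state that the TEE arm has no intraprocedural or postprocedural imaging; it names none.

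**Step 2: what adjudication can do.** The committee receives suspected events. It can reject an effusion as not major, which lowers the ICE count. It cannot raise the TEE count by effusions that nobody saw.

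**Step 3: possible size.** The protocol gives no effusion rate, detection probability or power for this endpoint, so there is no stated figure to reproduce. The only input from the document is 1810 patients randomised 1:1 (section 2.3), that is 1810 / 2 = 905 per arm. Everything else is assumed:

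- clinically evident effusion or tamponade: c = 0.8% in both arms
- true silent effusion rate: q = 0.5% to 3%, equal in both arms
- share of silent effusions found: 95% in the ICE arm, d = 10% to 80% in the TEE arm

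Formulas:

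- recorded rate, ICE: p1 = c + 0.95q
- recorded rate, TEE: p2 = c + dq
- spurious RR = p1 / p2
- probability of p<0.05: normal approximation to the two-sided chi-square test, with the pooled standard error for the critical value and the unpooled one for the sampling distribution

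Example with q = 2%, d = 30%:

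- p1 = 0.008 + 0.95 × 0.02 = 0.027, expected count 905 × 0.027 = 24.4
- p2 = 0.008 + 0.30 × 0.02 = 0.014, expected count 905 × 0.014 = 12.7
- RR = 0.027 / 0.014 = 1.93
- pooled SE = √(2 × 0.0205 × 0.9795 / 905) = 0.00666; unpooled SE = √((0.027 × 0.973 + 0.014 × 0.986) / 905) = 0.00665
- (0.013 − 1.96 × 0.00666) / 0.00665 ≈ −0.01, so the probability is about 50%

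Full grid. Each cell gives the expected TEE count, the spurious RR and the probability of p<0.05:

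| q | ICE count | d = 10% | d = 30% | d = 50% | d = 80% |
|---|---|---|---|---|---|
| 0.5% | 11.5 | 7.7; 1.50; 14% | 8.6; 1.34; 10% | 9.5; 1.21; 7% | 10.9; 1.06; 5% |
| 1% | 15.8 | 8.1; 1.94; 35% | 10.0; 1.59; 21% | 11.8; 1.35; 12% | 14.5; 1.09; 6% |
| 2% | 24.4 | 9.1; 2.70; 77% | 12.7; 1.93; 50% | 16.3; 1.50; 25% | 21.7; 1.125; 7% |
| 3% | 33.0 | 10.0; 3.32; 95% | 15.4; 2.15; 73% | 20.8; 1.59; 39% | 29.0; 1.14; 8% |

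With equal detection, the RR is 1.00 and the probability is the nominal 5%. The lower right of the grid is close to that; the lower left is far from it.

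**Step 4: masking.** In a simpler model, let the ICE arm find all effusions and the TEE arm a share s. The observed RR is then the true RR divided by s. A true RR of 0.50 with s = 0.50 appears as 0.50 / 0.50 = 1.00.

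**The case against.** **Silence is not absence.** A reader might infer that TEE-arm patients are ablated with no ultrasound at all, so that silent effusions there cannot be recorded. The protocol does not say this. It says that puncture is guided by fluoroscopy and names no effusion check. Sites may image the pericardium anyway, and at 80% detection the distortion is small throughout the grid. This stands, and is why the bias is stated conditionally.

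**The threshold may exist elsewhere.** Effusions appear under a heading of major bleeding, section 5.1 has no separate effusion item, and the committee works to a charter that is not at hand; a separate analysis plan may also exist. A clinical threshold in any of these would remove much of the excess from trivial effusions found by ICE. This also stands, so it would be too strong to say that adjudication cannot help. But the protocol's own definition has no threshold, and adjudication can correct only one side of the imbalance.

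**The numbers are assumed.** Correct. They show a range and do not estimate the bias.

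**The endpoint is secondary and the bias runs against the tested strategy.** Both are true. The bias would not produce a falsely favourable safety claim for ICE through excess detection. It could still produce a false harm signal or hide a real benefit. Tamponade would usually declare itself clinically in both arms, so that component is little affected.

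**Conclusion.** The concern holds in conditional form. The protocol combines an effusion endpoint without a severity threshold with effusion monitoring specified in one arm only. If the TEE arm has no equivalent imaging, the relative risk for major bleeding is biased against ICE and cannot be read simply as a difference in safety.

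The size cannot be derived from the document. Under the assumptions listed, the spurious RR lies between about 1.06 and 3.3, and the chance of p<0.05 without a true difference between about 5% and 95%. A negligible effect is as compatible with the text as a large one. The documents do not support saying that the comparison is certainly or heavily biased. The primary thromboembolic endpoint is not affected.

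**What to change.** In section 3.5, restrict the between-arm comparison of major bleeding to cardiac tamponade and pericardial effusions with haemodynamic compromise, which would come to light clinically in both arms.

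Report all other effusions descriptively by arm, with how each was found, outside the relative-risk comparison. This group includes effusions treated only because imaging showed them. An intervention alone should not qualify an effusion for the comparison: operators are unblinded, and an effusion seen on ICE can prompt an action that an unseen one would not.

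Have the blinded committee apply this definition before any unblinded look at the data. If the TEE arm does have an effusion assessment, or the committee's charter a threshold, the protocol should say so.

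Cost: fewer counted events, hence a wider interval. One eCRF item on how each effusion was found is also needed. It may have to be completed retrospectively, since section 3.2 already speaks of 1810 patients as recruited.

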## 4. Methods: Assignment of Interventions

### 4.1 Allocation

This study employs a **simple computerized randomization** strategy with a 1:1 allocation ratio. Eligible participants are randomly assigned to undergo thrombus screening with either ICE (ICE group) or TEE (TEE group) before catheter ablation.

The randomization schedule is generated using validated, centralized computer software to ensure adequate allocation concealment. Allocation occurs **after patient enrollment and informed consent**, and prior to the start of imaging and ablation procedures.

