### 79 **1.2 Trial Registration**

- 80 • Primary Registry: ClinicalTrials.gov
- 81 • Trial Identifying Number: NCT05466266
- 82 • Date of Registration: 2021-12-15
- 83 • Scientific Title: Comparison of Peri-procedural Complications of Intracardiac
- 84 Echocardiography and Transesophageal Echocardiography in Patients With
- 85 Atrial Fibrillation (ICE vs TEE Study)
- 86 • Public Title: ICE vs TEE Study
- 87 • Countries of Recruitment: China
- 88 • Health Conditions Studied: Atrial Fibrillation
- 89 • Intervention(s):

- 90 1. ICE group: Intracardiac echocardiography for LAA thrombus screening
- 91 2. TEE group: Transesophageal echocardiography for LAA thrombus
- 92 screening

- 93 • Study Type: Multicenter, randomized, open-label, parallel-group, non-
- 94 inferiority trial
- 95 • Target Sample Size: 1810 participants
- 96 • Start Date of Enrollment: August 2022

97

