### 3. Methods: Participants, Sample size justification , Interventions, and Endpoints

#### 3.1 Study Setting

This multicenter study was conducted at 10 tertiary medical institutions across China, including Shanghai Chest Hospital, Ren Ji Hospital, and eight additional high-volume centers specializing in AF ablation (see Appendix for full list of participating sites). All centers possess substantial expertise in AF ablation and intracardiac imaging, thereby ensuring strict adherence to the study protocol and high procedural quality.

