### 4.3 Implementation

- The randomization sequence is generated centrally by the study's data coordination center.
- Site investigators are responsible for enrolling eligible participants and confirming inclusion/exclusion criteria.

415       • Random assignment is implemented electronically through the electronic data  
416       capture (EDC) system, which automatically provides allocation after patient  
417       registration.

418 All randomization actions are timestamped and logged within the EDC system to  
419 ensure traceability and compliance.

420

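### Neither the simple randomisation nor the stated secondary analyses use centre, which gives up some precision on endpoints likely to vary between the ten hospitals

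*Protocol*

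**What the plan says.** Section 4.1 (Allocation) specifies "simple computerized randomization" as a "strategy with a 1:1 allocation ratio". Neither section 4.1 nor section 4.3 names a stratification factor, a block or a minimisation factor.

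Section 4.3 (Implementation) says that "The randomization sequence is generated centrally by the study's data coordination center", and assignment is delivered automatically by the EDC system once a patient is registered. Section 3.1 gives the setting: "This multicenter study was conducted at 10 tertiary medical institutions across China". Section 1.2 gives "Target Sample Size: 1810 participants".

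The secondary endpoints in section 3.5 include "Procedural characteristics: total procedure time, fluoroscopy time, and radiofrequency delivery time", along with hospitalisation cost and waiting time before the procedure. For the ICE arm, section 3.4 leaves the amount of fluoroscopy to the operator: "Minimal fluoroscopy was utilized at each step as determined feasible".

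Section 5.4 (Secondary Endpoint Analysis) names the t-test or Wilcoxon rank-sum test for continuous endpoints and chi-square or Fisher's exact test for categorical ones. Effects are reported as mean differences and relative risks. No centre term is mentioned.

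**The concern.** Simple randomisation balances the arms over the whole trial but leaves the split inside each hospital to chance. If an endpoint differs between hospitals, an uneven split carries part of that difference into the comparison of arms. Hospital pricing, waiting lists and operator habits make this plausible for cost, waiting time, procedure time and fluoroscopy time.

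Two steps could remove this noise: balancing arms within centre at allocation, or accounting for centre in the analysis. The protocol specifies neither. At stake is the width of the confidence intervals for the secondary endpoints on workflow and cost, which bear on the protocol's stated aim of improving procedural workflow.

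**Working it through.** **Inputs.** From the protocol: 1:1 simple randomisation (4.1), ten centres (3.1), N = 1810 (1.2), recruitment need of 1786 or about 893 per group (3.2), and expected event rates of 0.6% and 0.5% (3.2). Assumed, because the protocol does not give them: the centre sizes and the share ρ of outcome variance that lies between centres.

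**1. Overall balance.** The plan's figure is 1786/2 = 893 per group. Under Binomial(1786, 0.5) the 95% range for one arm is 852 to 934, and at N = 1810 it is 863 to 947. This agrees with the plan's approximate figure. An 863:947 split keeps 4 × (863/1810) × (947/1810) = 99.8% of the efficiency of an exact 1:1 split.

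**2. Balance within centres.** With ten equal centres of 1810/10 = 181 (assumed):
- The 95% range for one arm is 77 to 104.
- P(split of 55:45 or worse) = 0.181 per centre. For at least one of ten, 1 − (1 − 0.181)^10 = 0.86.
- P(split of 60:40 or worse) = 0.007 per centre, and 0.07 for at least one of ten.
- In a centre of 50 patients (assumed) the 95% range is 18 to 32.

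**3. What this costs on a continuous endpoint.** Write w for each centre's share of patients, and scale the outcome so that between-centre plus within-centre variance is 1. Under simple randomisation the variance of the unadjusted mean difference is about (4/N) × (1 − ρ·Σw²). With a centre term it is about (4/N) × (1 − ρ). The relative reduction is

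1 − (1 − ρ)/(1 − ρ·Σw²).

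For assumed sizes 500, 350, 250, 200, 150, 120, 90, 70, 50 and 30 (total 1810), Σw² = 528,300/1810² = 0.161.

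| Assumed ρ | Formula | Reduction | Simulation |
|---|---|---|---|
| 5% | 1 − 0.95/0.992 | 4.2% | about 3% |
| 10% | 1 − 0.90/0.984 | 8.5% | about 8% |
| 20% | 1 − 0.80/0.968 | 17.3% | about 18% |
| 30% | 1 − 0.70/0.952 | 26.4% | about 27% |

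The two columns agree to within simulation error. In interval width, the range runs from 1 − √0.97 = 1.5% narrower to 1 − √0.73 = 15% narrower. These figures are for mean differences. The gain for rank tests and binary endpoints was not computed.

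**4. Allocation or analysis?** In simulation with the same centre sizes, simple randomisation analysed with a centre term had essentially the same variance as allocation stratified by centre (ratio 1.00 to 1.01 for ρ from 5% to 30%). Two results on coverage of the 95% interval follow:
- Simple randomisation, unadjusted analysis: about 95%. The stated method is valid.
- Stratified allocation, unadjusted analysis: about 96% to 97% for ρ of 10% to 30%. The estimate is more precise but the interval does not show it.

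**5. Primary endpoint.** Expected events are 905 × 0.006 + 905 × 0.005 = 5.4 + 4.5, or about 10. Suppose the true risk varies between centres with an SD of 0.2 to 0.4 percentage points (assumed). The patient-level variance is about 0.0055 × 0.9945 = 0.00547, so centre explains 0.002²/0.00547 = 0.07% to 0.004²/0.00547 = 0.3% of it. There is almost nothing to gain.

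**The case against.** **Simple randomisation is valid, and at this size overall balance is secure.** This stands. A reader might infer from the 86% figure that the comparison is compromised. It is not: a 55:45 split within a centre still keeps 4 × 0.55 × 0.45 = 99% of 1:1 efficiency, and the unadjusted interval already allows for between-centre variation.

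**The gain belongs to the analysis, not to the allocation method.** This also stands, and it is why the remedy is directed first at section 5.4. A statistical analysis plan that is not shown might add a centre term. However, the protocol does not leave the method open: it names unadjusted tests for the secondary endpoints, and the point is about those.

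**Stratified blocks are not free.** This stands. The trial is open-label and site investigators enrol the patients, so blocking within sites makes the next assignment easier to guess, most of all in small centres. Unrestricted allocation is the least predictable scheme. Choosing between the two is a trade-off.

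**The evidence for centre effects is indirect.** This stands in part. Operator discretion over fluoroscopy is described for the ICE arm, and the two echocardiography platforms in section 3.4 are in the TEE arm. Neither shows a centre effect shared by both arms. That cost, waiting time and procedure time vary by hospital is a reasonable inference, but the protocol gives no figure for it.

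**A reader might also infer that within-centre balance is the only practical protection for the primary endpoint.** The documents do not support this. With about 10 expected events a regression with ten centre terms is not workable, but a Mantel-Haenszel stratified risk difference needs no parameter per centre. In any case, centre can explain very little of the variance of so rare an outcome.

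**Conclusion.** The point holds as one of efficiency on the secondary endpoints. As written, neither the allocation nor the stated secondary comparisons use centre, and a better method is available from data the trial already holds. The avoidable variance on a continuous endpoint is about 3% to 27% for assumed centre shares of 5% to 30% and the assumed unequal centre sizes. If centre effects are small, the loss is trivial. There is no bias or invalid test, the required sample size does not change, and the effect on the primary risk difference is negligible.

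**What to change.** **Analysis (the main change).** In section 5.4, Secondary Endpoint Analysis, replace the unadjusted comparisons by centre-stratified ones:
- Continuous endpoints: a linear model with arm and centre for the mean difference, or the van Elteren test where a rank test is wanted.
- Binary endpoints with enough events: the Mantel-Haenszel relative risk stratified by centre. Sparse endpoints can keep the exact test.

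The effect measures stay as the protocol states them (mean difference and relative risk). The cost is a few sentences and a variable already recorded. The change should be fixed before data are examined by arm, and it works whether or not enrolment is complete.

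**Allocation (optional, only if enrolment is still open).** The version date (July 2022) precedes the stated enrolment start (August 2022), but parts of the text describe randomisation and recruitment in the past tense, so the status is unclear. If patients are still being enrolled, the central EDC could stratify by centre with undisclosed, randomly varying block sizes, or use minimisation with a random element. The cost is a configuration change, one protocol sentence and somewhat more predictable assignment. Centre must still be in the analysis, because otherwise the unadjusted intervals would be too wide.
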